## Abstract

**Background:** Metabolic bariatric surgery is a highly effective and long-lasting treatment for obesity and related chronic conditions. Women of reproductive age represent the largest group undergoing these procedures. Observational studies suggest an increased risk of preterm birth and impaired foetal growth in this population, though the underlying mechanisms remain unclear. A key hypothesis is that altered glucose metabolism, characterised by frequent hypoglycaemia and glycaemic fluctuations, may contribute to these adverse outcomes. While glycaemic variability following metabolic bariatric surgery has been documented, its pattern during pregnancy and impact on pregnancy outcomes are still underexplored. **Methods:** In this Belgian multicentre prospective cohort study, we will investigate glycaemic patterns during pregnancy in women who have undergone metabolic bariatric surgery. Women aged 18–45 years with a confirmed singleton pregnancy up to 11 weeks and 6 days and a history of Roux-en-Y gastric bypass or sleeve gastrectomy will be eligible for inclusion. Women with pregestational diabetes or those taking medication known to interfere with glucose metabolism will be excluded. All participants will receive blinded continuous glucose monitoring (Dexcom^®^ G6) for a 10-day period at four time points throughout the pregnancy. Foetal body composition and growth will be measured during routine ultrasound; skinfolds will be measured in the neonate. The primary outcome is the association between mean glycemia and glycaemic variability on continuous glucose monitoring and birth weight. The planned sample size is ninety-five women. Linear mixed models for repeated measurements will be used for analysis. Confounders such as smoking, micronutrient deficiency, and surgery-to-conception interval will be added to the model as covariates. In a second exploratory phase, each participant in the surgical group will be matched with a control participant—without a history of metabolic bariatric surgery—based on pre-pregnancy BMI and age. Control participants will undergo the same study procedures, allowing for exploratory comparison of glycaemic patterns and other study outcomes. **Discussion:** This prospective longitudinal study will be the largest study using continuous glucose monitoring to investigate glucose metabolism during pregnancy after metabolic bariatric surgery and its impact on foetal growth and newborn body composition. **Trial registration**: ClinicalTrials.gov: NCT05084339. Registration date: 15 October 2021.

## 1. Background

Obesity is associated with increased risks for miscarriages, gestational diabetes mellitus (GDM), preeclampsia, and caesarean delivery [1]. Metabolic and bariatric surgery (MBS) is the most effective treatment for obesity and its related comorbidities [2]. Of all patients who undergo MBS, up to 80% are women of childbearing age [3]. As such, pregnancies in women with a history of MBS are becoming increasingly prevalent. Surgically induced metabolic changes benefit mother and child but can also lead to adverse pregnancy outcomes. Several nationwide register-based cohort studies and systematic reviews have shown that MBS is associated with lower risks for macrosomia, GDM, and hypertensive disorders, but with increased rates of small-for-gestational-age (SGA) infants, preterm delivery, and perinatal mortality [4,5,6,7,8]. Children born SGA are at an increased risk of developing type 2 diabetes and cardiovascular diseases in the long-term [9]. The fact that the increased risks of SGA and preterm deliveries remain when matching for pre-pregnancy weight suggests that MBS as such is associated with adverse obstetric outcomes, and not only through weight reduction [7]. A continuous decline in foetal growth throughout pregnancy has been demonstrated after Roux-en-Y gastric bypass (RYGB), starting at the beginning of the second trimester [10]. In addition, the foetal abdominal subcutaneous tissue thickness (FASTT) was markedly decreased in foetuses of mothers with a history of MBS [11].

The underlying mechanisms of foetal growth restriction in this population remain unclear but are likely multifactorial. Potential contributors include nutrient deficiencies, placental dysfunction, altered glucose metabolism, and potentially changes in other metabolic pathways. A prospective cohort study including 54 women with previous MBS confirmed reduced foetal growth in pregnancies following surgery and evaluated fetoplacental Dopplers as a proxy for placental function [12]. However, no alterations in fetoplacental circulation or correlations with foetal size were observed [12].

Evidence increasingly indicates that maternal metabolites beyond glucose contribute to foetal growth and newborn adiposity [13]. Metabolomics, the comprehensive analysis of metabolites in biological samples, enables the identification of metabolic biomarkers and the elucidation of mechanisms underlying early-life risk for conditions such as SGA, obesity, and T2DM [13]. The maternal metabolome undergoes temporal changes during pregnancy, resulting in stage-specific metabolite profiles [14]. Recent evidence suggests that maternal concentrations of amino acids, acylcarnitines, lipids, and fatty acids and their metabolites are associated with foetal growth and adiposity, independent of maternal BMI (body mass index) and glycaemia [13]. A systematic review assessing metabolomic predictors of SGA identified fatty acids, phosphosphingolipids, and amino acids as the most commonly reported predictive subclasses [15]. However, studies investigating metabolomic profiles in relation to foetal growth among pregnant women following bariatric surgery remain limited. One small study (25 RYBG and 8 SG) reported significantly lower third trimester serum concentrations of branched-chain and aromatic amino acids, as well as unsaturated lipids in the RYGB group [16]. These metabolite reductions were inversely associated with offspring birthweight [16].

The Pedersen’s hypothesis traditionally links maternal hyperglycaemia to increased foetal growth via foetal hyperinsulinemia—a concept confirmed by the Hyperglycaemia and Adverse Pregnancy Outcomes (HAPO) study, which demonstrated a continuous association between maternal glucose levels and increased birth weight [17]. Conversely, maternal hypoglycaemia—as observed in altered glucose dynamics following MBS—may contribute to foetal growth restriction by limiting glucose availability [18]. A retrospective study in a non-bariatric surgery population confirmed a significant association between hypoglycaemia during OGTT and low birth weight [19]. Similarly, in the MBS population, a small study has shown that women with reactive hypoglycaemia on OGTT had significantly higher rates of SGA infants [20]. A prospective cohort study investigated glucose metrics in 23 pregnant women with RYGB and 23 BMI- and parity-matched pregnant controls using continuous glucose monitoring (CGM) during the first, second, and third trimester, as well as early postpartum [21]. The study found a slight increase in time spent in the low glycaemic range among pregnancies resulting in SGA infants. However, the study was not sufficiently powered to detect significant differences in this outcome.

The main aim of this multicentric prospective study is to determine whether altered glucose metabolism (including lower blood glucose levels, increased time spent in hypoglycaemia, and glycaemic variability) measured by CGM in pregnancy after MBS is related to impaired foetal growth.

## 2. Methods

### 2.1. Study Design and Setting

The GLORIA study is a prospective cohort study involving eight Belgian sites, investigating pregnancy outcomes following sleeve gastrectomy (SG) or RYGB. In a second stage, outcomes will be compared to a matched control group using an exploratory approach. SG has increasingly become the first-choice type of MBS for women of reproductive age. We estimate that between 30 and 50% of participants will have SG in the study. For each participant in the surgical cohort, an age- (≤2 years difference, and age > 40 will be rounded to 40 years) and BMI-matched (≤2 BMI points difference, matched to pre-pregnancy BMI) pregnant woman without history of MBS will be recruited. Seven Belgian hospitals were originally included to take part in the study: three university hospitals (UZ Leuven, UZ Antwerpen, and UZ Gent) and four large non-university hospitals (ZAS Palfijn, AZORG Aalst, Imelda Bonheiden, and AZ St-Jan Brugge). In 2023, one additional centre was added. All eight centres have previously participated in multicentre studies initiated by our research group [22,23]. Participating centres were selected for their expertise in endocrinology research, as well as obstetrical management of pregnant women with a history of MBS.

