#### 2.4.1. Inclusion Criteria

-age 18–45 years-singleton pregnancy with ultrasound-confirmed gestational age up to eleven weeks and six days-for the group with MBS: history of SG or RYGB-participants need to speak and understand Flemish, French, or English and have e-mail access

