#### 2.5.2. Control

Pregnant women with no history of MBS who meet the inclusion criteria can participate if matched with a participant from the surgical group. Controls will be manually matched 1:1 based on age and pre-pregnancy BMI in early pregnancy (before twelve weeks).

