##### Exploratory Comparative Analyses

The control group will be manually matched in a 1:1 ratio based on age and pre-pregnancy BMI before participation. A comparison of both groups on participant characteristics such as parity, insufficient GWG, hypertension, micronutrient deficiencies, and smoking status will be performed using Fisher exact tests. The comparison between the MBS and control group on birth weight and glycaemic measures will be performed using linear mixed models with a random intercept to account for clustering by matching. Confounders will be included as covariates in the model in case they were shown to differ between groups. Group comparisons on binary variables such as adverse pregnancy outcomes will be performed using a similar approach, applying generalised linear mixed models for binary responses.

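### Capping age at 40 lets a matched pair be up to 7 years apart, and the exploratory MBS-versus-control models do not commit to adjusting for age or BMI

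*Protocol article*

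**What the plan says.** Section 2.1 gives the age rule in one parenthesis: a difference of at most 2 years, with the addition that "age > 40 will be rounded to 40 years". The BMI rule has no such cap: "≤2 BMI points difference, matched to pre-pregnancy BMI". Section 2.4.1 sets eligibility at "age 18–45 years".

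The analysis of the matched comparison is in section 2.9.2, under Exploratory Comparative Analyses. It opens by restating the design: "The control group will be manually matched in a 1:1 ratio based on age and pre-pregnancy BMI before participation". The groups are then compared, using Fisher exact tests, on "participant characteristics such as parity, insufficient GWG, hypertension, micronutrient deficiencies, and smoking status". The models carry a random intercept for the matching, and the covariate rule is: "Confounders will be included as covariates in the model in case they were shown to differ between groups".

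Sections 2.1, 2.3 and 2.9.2 all label the comparison with controls as exploratory. Section 2.3.1 confines the primary outcome to the surgical group.

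**The concern.** Age and pre-pregnancy BMI are the only two matching factors, and both plausibly relate to glycaemia, GDM and birth weight. A reader who sees a 2-year caliper will take age as closely balanced within every pair. With the cap this holds only when neither woman is over 40.

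Looser matching at the top of the age range would matter little if the model adjusted for true age. The stated rule does not ensure that. It makes adjustment depend on a demonstrated group difference, and the one test named for the purpose is meant for categorical characteristics, so it does not suit continuous age or BMI. A gap confined to a few older pairs would also hardly show in a comparison of whole groups. Any residual difference would then stay in the MBS-versus-control estimates.

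**Working it through.** **Inputs.** Caliper of 2 years and cap at 40 (section 2.1); eligible ages 18 to 45 (section 2.4.1); planned surgical cohort of 95 (section 2.9.1). The share of women over 40 is not given, so it is varied below.

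**The stated caliper.** Take whole-year ages *a* and *b* from 18 to 45. Without the cap, a pair is allowed if |*a* − *b*| ≤ 2, and the largest true gap is 2 years. With the cap, it is allowed if |min(*a*, 40) − min(*b*, 40)| ≤ 2. On the capped scale every allowed pair is within 2 years, so the plan's figure is reproduced on its own scale.

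**The true gap under the cap.** For one woman aged 45: min(45, 40) = 40, so her partner's capped age must be at least 38. A 38-year-old is allowed, and 45 − 38 = 7. A woman over 40 may have a partner of any age from 38 to 45, so her largest gap is max(*a* − 38, 45 − *a*). Enumerating all pairs gives:

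| Age of one member | Allowed partner ages | Largest true gap (years) |
|---|---|---|
| 36 | 34–38 | 2 |
| 37 | 35–39 | 2 |
| 38 | 36–45 | 7 |
| 39 | 37–45 | 6 |
| 40 | 38–45 | 5 |
| 41 | 38–45 | 4 |
| 42 | 38–45 | 4 |
| 43 | 38–45 | 5 |
| 44 | 38–45 | 6 |
| 45 | 38–45 | 7 |

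Below age 38 the gap never exceeds 2 years. Of 164 allowed ordered age combinations, 30 exceed 2 years; each has one member aged 41–45 and the other at least 38. Where both women are over 40, the gap is at most 4 years, and 19 of the 25 combinations are within 2. These are counts of combinations, not of women. If age is taken in fractions and 45 runs to the next birthday, the maximum is just under 8 years (45.99 − 38 = 7.99).

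**Why the pair intercept does not help.** For pair *i*, write the outcome as *Y* = μ + δ·MBS + β·age + *u*ᵢ + error, where *u*ᵢ is the pair intercept. The within-pair difference is δ + β·(age of surgical woman − age of control) + error. The term *u*ᵢ cancels but the age gap does not, so if age is left out the estimate of δ is shifted by β times the mean within-pair gap. The same holds for BMI.

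**Size for age.** Let *p* be the share of surgical women over 40. The worst case makes all of them 45, pairs each with a 38-year-old, and sets the mean gap in all other pairs to zero. The mean shift is then 7 × *p*:

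- *p* = 1% (95 × 0.01 ≈ 1 woman): 7 × 0.01 = 0.07 years
- *p* = 5% (95 × 0.05 ≈ 5 women): 7 × 0.05 = 0.35 years
- *p* = 10% (95 × 0.10 ≈ 10 women): 7 × 0.10 = 0.70 years

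The shift in any outcome is β times these values. The article gives no β.

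**The case against.** The cap stands in the same parenthesis as the caliper. It is one disclosed rule and a sensible way to keep older women matchable, and nothing in it contradicts itself. A reader might infer that the 2-year caliper is broken or that older pairs are not age-matched at all. The text does not support either: the caliper is openly widened, and any partner of a woman over 40 must be at least 38.

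A reader might also infer that age and BMI are definitely left unadjusted. That is too firm. The list of compared characteristics is open, neither factor is excluded, and an analysis plan that is not shown may name both. This stands. What remains is that the article does state a covariate rule, and a difference-triggered rule suits matching factors badly.

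It is tempting, too, to claim that controls will be systematically younger. If control ages were normal with mean 30 to 32 and SD 4.5 to 5, the expected control would be about 1, 3 and 5 years younger than surgical women aged 41, 43 and 45. But those distributions are assumed and imply random choice within the window, whereas matching is manual from a log and a closer control can be picked. The rule is also symmetric: a surgical woman of 38 to 40 may receive a control of 41 to 45. A consistent direction is not established.

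For BMI, whatever difference remains inside the 2-point limit is the ordinary residue of caliper matching. It is not a consequence of the age cap or a fault in the plan.

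**Conclusion.** The point holds as a minor one. For pairs that include a woman over 40, the effective age caliper is as wide as 7 years, and the analysis text gives no commitment to adjust for exact age or BMI. The 7-year figure follows from the article's own rules in whole years. The effect on the group contrast is small: at most 0.07 to 0.70 years in mean age if 1% to 10% of 95 women are over 40, and real pairs would give less. That range rests on the assumed share and on an extreme pairing. The primary and secondary analyses, which use the surgical group only, are unaffected. The change is worth making because it costs almost nothing.

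**What to change.** In section 2.9.2, Exploratory Comparative Analyses, add a sentence to this effect: *every MBS-versus-control model will include exact (uncapped) age and exact pre-pregnancy BMI as continuous fixed covariates, regardless of any test for a difference between groups.* The existing rule can stay for the other characteristics.

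Leave the matching rule unchanged. Section 2.1 already states the cap, and tightening the caliper above 40 would trade balance against recruitment for little gain.

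The cost is one sentence and two covariates. Section 2.8.1 says the matching log holds age and BMI for all participants; the only check is that true age, not the capped value, reaches the analysis file. No extra participants or measurements are needed.

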### 2.2. Modifications to the Study Protocol

One more study site was added to participate in the study (AZ Groeninge Kortrijk) to facilitate recruitment. This has led to an amendment which was approved by the central ethics committee on 17 August 2023.

### 2.3. Objectives

This trial is designed to show with 80% power a linear association between mean glycemia or glycaemic variability and birth weight in a pregnancy after MBS. The hypothesis is that an altered metabolic profile including an altered glucose metabolism (with increased time spent in hypoglycaemia and greater glycaemic variability) and altered metabolomics during pregnancy after MBS contribute to the increased risk of adverse pregnancy outcomes such as SGA and preterm delivery. In addition, we hypothesise that concentrations of branched-chain and aromatic amino acids, and unsaturated lipids in the third trimester of pregnancy, are lower in pregnant women with MBS, and that this is also associated with a lower birth weight.

This study aims to evaluate whether biomarkers derived from CGM and metabolomic profiling in pregnancies following MBS are associated with foetal growth and newborn body composition.

The following specific aims will be addressed.

Primary aim: To determine whether altered glucose metabolism (including lower mean blood glucose levels, hypoglycaemia, and glycaemic variability) measured by CGM in pregnancy after MBS is related to delayed foetal growth.

Exploratory objectives:To compare glucose metabolisms between pregnant women after MBS and age- and BMI-matched pregnant women without MBS.To determine whether metabolic alterations are associated with delayed foetal growth in pregnant women after MBS compared to pregnant women without MBS, and, in particular, which metabolites are related to adverse outcomes in pregnancy.To determine whether there are differences in glucose metabolism and other metabolites (by using metabolomics) between RYBG and SG.To determine the impact of MBS on the body composition of newborns.To determine the accuracy of CGM compared to the self-monitoring of capillary blood glucose (SMBG) to screen for GDM in pregnant women with MBS.

#### 2.3.1. Primary Outcome

In the surgical group, we will assess mean glycaemia as a continuous outcome variable, glycaemic variability (standard deviation) as a continuous outcome variable, and birth weight as a continuous explanatory variable. Linear mixed models will be used for the primary outcome analysis. The outcome variables will be measured at four time points for each subject. Confounders will be added to the model as covariates.

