-Maternal glycaemic outcomes: percentage of time < 54 mg/dL (ADA recommendations of the definition of hypoglycaemia) [24]; glycaemic variability metrics: standard deviation (SD), Coefficient of Variation (CV) and Mean Amplitude of Glucose Excursions (MAGE); percentage of time > 120 mg/dL; percentage of time > 140 mg/dL; percentage of time > 180 mg/dL; percentage of time < 70 mg/dL; percentage of time < 63 mg/dL; percentage of time < 50 mg/dL; low blood glucose index (LBGI)-Maternal pregnancy outcomes: duration of pregnancy; time from surgery to conception; prevalence of micro- and macronutrient deficiencies; body composition in early pregnancy as assessed by bio-impedance measurement, prevalence of GDM; gestational weight gain (GWG); prevalence of caesarean section; prevalence of pre-eclampsia and eclampsia, prevalence of gestational hypertension; surgery-related complications during pregnancy; type of labour; type of delivery; complications during delivery-Foetal growth and body composition outcomes: prevalence of SGA; large for gestational age (LGA); prevalence of intra-uterine growth retardation (IUGR); FASTT; pregnancy loss-Neonatal outcomes: body composition of the newborn assessed by skin fold thickness measurements, according to [25]; prevalence of preterm delivery; prevalence of neonatal hypoglycaemia; prevalence of neonatal intensive care unit (NICU) admission; foetal malformation; complications during delivery; sex of the infant; birth weight, length, and percentile; neonatal death-Identification of new biomarkers: metabolomics on maternal plasma collected at 30–34 weeks: lipid omics platform and metabolism and energy platform. We will prioritise analyses for the surgical group.-Patient-reported outcomes: certain potential confounders, such as smoking status, will be derived from survey data. Additionally, other patient-reported outcomes collected through the surveys will be analysed as independent outcomes in the exploratory comparisons between subgroups. The following questionnaires will be completed at the different study visits:A self-designed questionnaire on general habits and socio-economic background previously used in the Belgian Diabetes in Pregnancy study (BEDIP) to extensively collect information on socio-economic status and habits [22].A self-designed questionnaire on the user-friendliness of the masked CGM, based on the CGM Satisfaction Scale (CGM-SAT) [26], the Glucose Monitoring Experiences Questionnaire (GME-Q) [27], and the Glucose Monitoring Satisfaction Survey (GMSS) [28].Frequency Food questionnaire (FFQ), including questions on frequency and portion size of consumed foods and beverages validated for the Belgian population [29].International Physical Activity Questionnaire (IPAQ, full version) validated for use in the Belgian population and as used in the BEDIP study [22]. This questionnaire assesses various domains of physical activity, including job-related tasks, caregiving, and time spent sitting.The 36-Item Short Form Health Survey (SF-36) includes a set of generic, coherent, and easily administered quality of life measures and is validated for use in the maternity context [30].The 20-item Centre for Epidemiologic Studies-Depression (CES-D) questionnaire, which is validated in pregnancy to asses symptoms of clinical depression over the past seven days [31].The State-Trait Anxiety Inventory (STAI) questionnaire, a validated six-item short-form on anxiety, which is validated for the Dutch speaking population [32].

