#### 2.9.2. Statistical Methods

##### Primary and Secondary Analyses (MBS Group)

The primary analysis will be performed using linear mixed models, adjusted for confounders. Mean glycemia refers to the mean interstitial glucose level measured via CGM throughout pregnancy. Glycaemic variability reflects fluctuations in blood glucose levels and is quantified using variables such as SD, CV, and MAGE derived from CGM. Repeated measurements will be used for the primary outcome analysis, with mean glycemia and glycaemic variability treated as continuous outcome variables, and birth weight as the explanatory variable. To account for clustering due to repeated measures, linear mixed models will be used with a random intercept for the subject. Confounders such as smoking, hypertension, nutrient deficiencies, insufficient gestational weight gain, and time from surgery will be added to the model as covariates to determine the independent association between birth weight and glycaemic parameters. Variables will be considered confounders if they are associated with both birth weight and glycaemic parameters. Linear slopes with 95% confidence intervals will describe the association between glycaemic parameters and birth weight. No specific action is taken to deal with missing CGM results given the fact that the analysis model is likelihood-based and known to provide unbiased results under the fairly general assumption of missingness at random [42]. Statistical analysis will be performed by SAS version 9.4; all tests will be two-sided with significance set at *p* < 0.05.

Secondary outcomes, including time spent <54 mg/dL and hyperglycaemic thresholds (>120 mg/dL and >140 mg/dL), will be analysed analogously.

Third, associations between glycaemic patterns and binary neonatal outcomes, including SGA and birth defects, will be assessed similarly using linear models for repeated measurements. Mean differences with 95% confidence intervals will be estimated between cases with and without the specified adverse outcome.

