## 3. Discussion

This large longitudinal cohort study aims to investigate whether pregnancy following MBS is associated with altered maternal glucose profiles, as assessed by CGM, and whether these alterations are linked to differences in foetal growth and newborn body composition. Outside of pregnancy, altered glucose patterns after MBS have been well-documented [18]. Emerging data suggests that pregnancies following RYGB are marked by significant glycaemic variability, including frequent episodes of both hyper- and hypoglycaemia. However, most studies to date are small and cross-sectional. Bonis et al. first reported wide glucose fluctuations and substantial hyperglycaemia in mid-pregnancy CGM profiles of post-RYGB women, resembling patterns seen in the non-pregnant post-RYGB population [40]. Leutner et al. similarly found increased glycaemic variability, including more frequent day and nighttime hypoglycaemic events compared to pregnant controls [41]. In a larger retrospective study, Gohier et al. found that 73% of women had abnormal time in range (TIR), and found associations between hypoglycaemia and prematurity, while SGA was paradoxically linked to lower hypoglycaemia exposure [44]. Additionally, an observational cross-sectional study comparing pregnancies after RYGB and SG found that while mean glucose levels were similar, women post-RYGB experienced greater glycaemic variability and spent less time in the target glucose range, indicating more pronounced glucose fluctuations following RYGB [45]. The only longitudinal data come from Stentebjerg et al., who performed CGM across all trimesters, demonstrating that, compared to BMI- and parity-matched controls, these pregnant women spent more time in both hyperglycaemia and hypoglycaemia. They also observed a modest association between increased time spent in hypoglycaemia and SGA outcomes [21]. Overall, while evidence points to a distinct glycaemic profile in post-RYGB pregnancies, none of these earlier studies were sufficiently powered to show the implications on foetal growth [21].

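### The aim is foetal growth, but the powered test uses crude birth weight, and the plan does not guarantee that gestational age or infant sex is accounted for

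*Protocol article*

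**What the plan says.** - **Aim.** Section 2.3 asks whether altered glucose metabolism "measured by CGM in pregnancy after MBS is related to delayed foetal growth". Section 2.9 restates this as a contribution to foetal growth restriction.
- **Variable tested.** Section 2.3.1 takes mean glycaemia and its standard deviation as outcomes, with "birth weight as a continuous explanatory variable". Section 2.9.2 repeats this, and the power statement in 2.9.1 also refers to birth weight. Nothing in the article standardises it for gestational age or sex.
- **Covariates.** Section 2.9.2: "Confounders such as smoking, hypertension, nutrient deficiencies, insufficient gestational weight gain, and time from surgery will be added to the model as covariates". Neither gestational age at delivery nor infant sex is named. The list is open, but the same paragraph then sets an entry rule: a variable qualifies only when it is linked to glycaemia as well as to birth weight.
- **Length of gestation.** The background reports "increased rates of small-for-gestational-age (SGA) infants, preterm delivery, and perinatal mortality" after surgery. The hypothesis in section 2.3 is that altered metabolism will "contribute to the increased risk of adverse pregnancy outcomes such as SGA and preterm delivery". Preterm births are not excluded.
- **Data collected.** Section 2.3.3 lists pregnancy duration and "sex of the infant; birth weight, length, and percentile", all as exploratory outcomes. SGA is a binary secondary outcome (sections 2.3.2 and 2.9.2).

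**The concern.** Birth weight has two components: how fast the foetus grew and how long it had to grow. Only the first is the stated aim. Infant sex shifts weight as well and tells us nothing about growth restriction.

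If gestational age and sex are unrelated to glycaemia, their share of birth-weight variance acts like measurement error in the explanatory variable: the slope flattens and power falls. If gestational age is related to glycaemia, as the study's own hypothesis about preterm delivery allows, part of the slope reflects length of gestation. The plan does not fix in advance which of these two slopes it will report. The answer depends on whether gestational age is looked at as a candidate and on whether it passes a check in about 95 women.

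The discussion also cites a retrospective study that "found associations between hypoglycaemia and prematurity, while SGA was paradoxically linked to lower hypoglycaemia exposure". That is one reason to keep the two components apart.

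**Working it through.** **Step 1. Reproduce the plan's own figure.** Inputs from section 2.9.1: effect size 0.3 (read as a correlation), 80% power, test-wise alpha 0.025, cluster size 4, ICC 0.5, 30% of measurements missing, four adjustment variables. Section 2.9.2 gives two-sided tests.

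- Independent observations, Fisher z: ((2.241 + 0.842) / atanh(0.3))² + 3 + 4 = (3.083 / 0.3095)² + 7 = 99.2 + 7 = 106.2
- Design effect: 1 + (4 − 1) × 0.5 = 2.5
- Women: 106.2 × 2.5 / 4 / 0.7 = 94.8, so 95
- Back-check: effective n = 95 × 4 × 0.7 / 2.5 = 106.4; power = Φ(0.3095 × √(106.4 − 7) − 2.241) = Φ(0.845) = 0.80

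The figure of 95 reproduces. The point concerns what is measured, not the sample size.

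**Step 2. What crude weight costs if gestational age and sex are unrelated to glucose.** Two assumptions are not in the article: that 0.3 is the correlation between glycaemia and growth for gestational age, and that gestational age plus sex carry a share R² of birth-weight variance. Then r(crude) = 0.3 × √(1 − R²), and power = Φ(atanh(r) × √99.4 − 2.241).

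| Assumed R² | r with crude weight | Power at 95 women |
|---|---|---|
| 0 | 0.300 | 80% |
| 10% | 0.285 | 75% |
| 30% | 0.251 | 62% |
| 50% | 0.212 | 46% |

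A second route starts from assumed grams: gestational-age SD 1.0 to 2.5 weeks, 120 to 180 g per week, a sex difference of 120 g and a residual SD of 400 g. Gestation then carries about 8% to 55% of the variance, r is 0.28 down to 0.20, and power is 75% down to 41%.

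**Step 3. Does the confounder rule remove the problem?** There are three cases.

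- *Infant sex.* It affects weight but has no evident link to maternal glucose, so it would probably fail the rule and stay in as noise. Its share is small: about 1% to 2% of variance under the gram assumptions above.
- *Gestational age unrelated to glucose.* It fails the rule and stays in as noise. This is the case in Step 2.
- *Gestational age related to glucose.* It meets the rule if it is screened. Take no growth effect, gestation carrying 40% of birth-weight variance, and a glycaemia–gestation correlation of 0.3 or 0.4. Never screened, r = 0.3 × √0.4 = 0.190 or 0.4 × √0.4 = 0.253, and the test rejects 37% or 63% of the time. Simulated with screening at p < 0.05 (an assumed threshold; 106 effective observations, four other covariates), gestational age is admitted in about 88% or 99% of runs, and rejection is about 3%, close to the nominal 2.5%.

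So where the rule is applied to gestational age, it largely controls false attribution. It does nothing for the loss of precision.

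**The case against.** - **The plan's rule can admit gestational age.** The covariate list is open, and Step 3 shows that the rule works in the very scenario where confounding would be serious. This stands. A reader might infer that a significant slope could arise wholly from earlier delivery, with rejection rates of 37% to 63%. Those rates hold only if gestational age is never screened as a confounder, and the article does not say that.
- **The 0.3 is stated for birth weight.** Section 2.9.1 powers an association with birth weight, not with an adjusted growth measure. This also stands. The article does not show that the study is underpowered for what it states. The loss in Step 2 is conditional on moving 0.3 to growth and on an assumed variance share.
- **Growth is examined elsewhere.** SGA, IUGR, FASTT, birth-weight percentile and preterm delivery are all listed outcomes, and a purely preterm effect should show as a weight slope without an SGA difference. This helps interpretation, but these analyses are secondary or exploratory, SGA is binary, and none is the powered test.
- **Gestational length may lie on the pathway.** Conditioning on it changes the question from total association to association with size for gestational age. That is true, but size for gestational age is what the aim describes, and gestational length can have its own analysis.
- **Opposing effects are not shown for the primary test.** The cited contrast between prematurity and SGA comes from one retrospective study of hypoglycaemia. The primary glycaemic variables here are mean and SD, so cancellation in the primary slope is possible but unsupported.
- **The article is condensed.** A fuller candidate-covariate list may exist. But the article itself fixes both the primary variable and the entry rule, and these two do not match the aim.

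**Conclusion.** The point holds as a mismatch between aim and variable, and should be fixed. The powered test uses crude birth weight for a question about growth. The covariate rule would probably exclude infant sex, excludes gestational age when it is unrelated to glucose, and otherwise leaves its entry to a check with no stated threshold.

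The likely cost is lost precision. On the assumptions in Step 2, power is about 75% at a 10% variance share and 46% at 50%, against the planned 80%. These are illustrations, since the article gives neither the variance share nor a correlation with growth.

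The documents do not support the stronger readings that the primary analysis cannot inform the growth question, or that it carries a false-attribution rate of 37% to 63%.

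**What to change.** Choose one of these before analysis:

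1. Make the birth-weight z-score for gestational age and sex the primary birth-weight variable, and name the reference chart; or
2. Keep birth weight in grams and prespecify gestational age at delivery and infant sex as fixed covariates, exempt from the confounder rule.

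In either case, report crude birth weight as a sensitivity analysis and analyse gestational length separately, because it may lie on the pathway from glycaemia to birth weight.

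**Cost.** No new data: pregnancy duration, infant sex and birth-weight percentile are already collected. With option 1, the sample size stays at 95 if 0.3 is taken for the z-score. With option 2, each extra covariate adds 2.5 / 4 / 0.7 = 0.9 woman, so two beyond the planned four give 94.8 + 1.8 = 96.6, or 97. The allowance of four needs checking anyway, since section 2.9.2 already names five confounders.

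**Downsides.** The estimand becomes size for gestational age. With option 1 a chart must be chosen and the slope is per SD, so an equivalent in grams should be given alongside.
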